#### Cardiorespiratory fitness

2.7.2

Cardiorespiratory fitness was assessed via a graded exercise treadmill test repeated at the same time of day for each repeat visit for a given individual, and was conducted by the same researcher. At baseline, this exercise test served the dual purpose of being a fitness test and a screening tool for inclusion in the training study, along with providing prescriptive information for the END training intervention. For the 2 h prior to the exercise test, participants were instructed to abstain from food and drinks other than water. Participant height (cm) and weight (kg) were recorded and they were then asked to stand on the treadmill. The graded exercise test protocol and Borg RPE scale [36] was explained to the participant. An automated blood pressure (BP) cuff (Dinamap V100, GE, Healthcare, USA) was fitted to the left arm and a HR monitor (Polar RS300X HR monitor, Polar Electro Oy, Finland) was fitted for recording of resting (upright) HR. Resting blood lactate was then extracted from the earlobe of the participant using a lancet, collecting the second droplet of blood in a lactate pro 2 (Lactate Pro2 LT-1730, Akryay USA). The participant was then fitted with a headframe, Hans Rudolph mouthpiece and nose clip. The two-way mouthpiece permitted subsequent analysis of continuous expired air using a metabolic cart (Parvomedics TrueOne 2400, Salt Lake City, UT) which was calibrated according to manufacturer specifications, using gases of known concentrations with a 3.0 L syringe prior to each test. The reliability for this cart (tested ~7 days apart) has been tested to produce a VO_2_max technical error of 0.15 L min, or 2.4%. Baseline resting steady state respiratory data (2 min) was collected with the participant standing stationary on the treadmill prior to commencing the graded exercise test. The treadmill starting speed was set at 8 kph and increased by 1 km/h each stage, while the gradient stayed at 1% throughout the test. Each stage was 3 min long, interspersed with a 1 min rest period. In the last 10s of each stage, HR was recorded and at the end of each stage, participants were instructed to brace their hands on the side railings of the treadmill and place feet on the stationary sides. This started the 1 min rest period between each stage where speed was immediately decreased to 2 km/h. A blood lactate and RPE for that stage were recorded before participants were instructed to step back onto the treadmill to walk at 2 kph until the 1 min rest period was complete whereupon the treadmill speed was then increased to the speed of the next stage. Standardised verbal encouragement was provided throughout the test to elicit maximal effort. The test was completed once the participant reached volitional exhaustion. Participants were able to terminate the test at any time by bracing and jumping off the treadmill or signalling to the researcher they wanted to stop.

#### Muscular strength

2.7.3

Maximal muscular strength was assessed according to a 1RM protocol, before and after each exercise intervention, as well as half way through the RES intervention so that exercise intervention weights could be appropriately progressed (for each individual within a twin pair). The reliability for upper and lower body 1RM performed ~7 days apart in healthy subjects has provided a high ICC (ICC > 0.99) and high correlation (r > 0.9) [37]. Participants arrived at the gym at the same time of day for each repeated testing session. Participants performed 1RM tests of bench press and leg press, conducted by the same researcher at each visit. These tests were chosen as they are considered relatively safe when performed with assistance of a qualified sport scientist for untrained individuals and incorporate the major muscle groups for both upper and lower body strength. Prior to participants starting their tests, the researcher demonstrated and explained correct lifting technique. The 1RM protocol included a warm up (five reps of 20 kg for bench press and ten reps of 60 kg for leg press), followed by five attempts to reach maximal muscular contraction in one repetition. There were 3 min breaks between efforts and weight was added depending on the participants reported RPE after each attempt. This process was repeated until the participant reported an RPE of 20, they failed to complete their repetition with correct technique, or the researcher deemed it necessary. Standardised encouragement was performed by the researcher to all participants during the test.

#### Physical activity

2.7.4

Total (TEE) and active (AEE) energy expenditure were measured throughout the study, pre-post each exercise intervention (weeks 0, 12, 24 and 36). The primary purpose of this was to examine whether the results obtained from the study were due to the exercise interventions that were conducted throughout the study, or external and incidental changes in TEE and AEE that occurred outside of the planned training sessions. Actiheart monitors (Actiheart 4, CamNtech Ltd, Cambridge, UK) were used to assess TEE and AEE as they include a combined HR and accelerometer, which have been shown to be valid in adolescents [38]. Participants were familiarised with the Actiheart monitors for use, care, skin preparation and instructed to wear the Actiheart for a period of 5 days, and not to wear whilst showering. They were also instructed to take the Actiheart off for sleep (“put Actiheart on first thing when they get up and take off when they get in to bed”) as we were interested in estimating TEE and AEE of participants normal daily activities. Actihearts were first placed on participants with two ECG electrodes (40 mm × 34 mm; AgCl, Red Dot 2560, 3 M) either above or below the nipple line with the medial electrode placed in the centre of the chest (usually on the sternum) and the lateral electrode placed horizontally to the left side with the wire straight but not taut. A signal test was first performed to determine the best positioning of the electrodes for each participant where a HR trace is best conducted. Electrode positioning was noted and repeated at subsequent timepoints. Following determination of the best site for each individual to wear their Actiheart for the desired days, a long-term test was set up which activated continuous recording over 1 min epochs. The Actiheart data was downloaded after each trial using a reader interface unit and analysed using Actiheart software (Actiheart software 4.0.65, CamNtech Ltd, Cambridge, UK). The main outcome measures collected were TEE, AEE and quantification of time spent in sedentary, light, moderate or vigorous physical activity according to METS [39,40].

#### Food diary and appetite

2.7.5

A food diary was administered to each participant along with some general trait appetite-related questionnaires (weeks 0, 12, 24 and 36) to complete the week prior to or immediately following each exercise intervention. Food diaries covered four consecutive days, with one having to be a weekend day, on participants ‘normal’ days of eating. Food diaries required participants to record the type, brand, cooking method, portion size and timing of ingested food and beverage in detail, for the purpose of assessing whether eating habits had remained constant throughout the study. Mean total daily energy intake, together with the quantity of carbohydrate, fat, and protein consumed were determined from these records using a commercially available software program (Foodworks 9; Xyris Software, Queensland, Australia). General appetite-related questionnaires included the food craving inventory – UK version (FCI-UK [41]), the compensatory eating motives questionnaire (CEMQ [42]), three factor eating behaviour questionnaire (3FEBQ [43]) and the trait general food cravings questionnaire (G-FCQ-TRAIT [44]). Participants were also administered two acute appetite questionnaires, the visual analogue scale (VAS) [45] and general food cravings questionnaire – state (G-FCQ-STATE) [44], at weeks 0, 12, 24 and 36 in a fasted state at the same time of the morning at each time point, and immediately prior to and after their graded exercise test. The VAS was also administered with the food diary and participants were required to complete a VAS for perceived appetite upon waking up in a fasted state, immediately prior to consuming lunch, dinner and going to bed.

#### Body composition

2.7.6

Body composition was measured using dual energy X-ray absorptiometry (Lunar iDXA, GE, healthcare, USA). Standard calibration and quality assurance procedures were used, in line with the equipment documentation (www3.gehealthcare.com). Outcome measures included regional and whole-body percent fat; grams of lean tissue, fat tissue, bone mineral content, visceral adipose tissue; gynoid and android fat percentages and ratios and bone mineral density. Participants arrived at the laboratory at the same time for each of the four measurements (pre- and post-each exercise intervention), usually in the afternoon/evening. Participants were instructed to fast for 3 h, be normally hydrated (i.e. not hyper/hypo-hydrated, or post exercise) and eliminated prior to the test. The inter- and intratester reliability results of our machine are very highly repeatable (ICC >0.99) in 52 tested participants [46].

#### Biochemistry

2.7.7

Participants arrived at the laboratory at the same time each morning for repeated measures following an overnight fast. Participants had refrained from any moderate/vigorous physical activity, alcohol and medication the 24 h prior to the testing session. This was confirmed at the start of each session verbally and recorded on the testing sheet. Assessments were conducted in a temperature, light and noise standardised room. These conditions were also adopted for the cerebrovascular blood flow and cognition, peripheral vascular blood flow, blood pressure and girths assessments. Blood was drawn from the antecubital fossa using a 21G needle by a trained phlebotomist in the UWA laboratory into five collection tubes (2× Vacuette by Greiner bio-one, Kremsmünster, AT; 3× Vacutainer, DB). Sterile techniques were applied, identical to those used in routine clinical services, and a maximum of 20 mL of blood was drawn per visit. Three blood tubes (2× lithium heparin, 1× fluoride oxalate) were analysed by a commercial pathology laboratory, for lipids (total cholesterol, triglycerides, low-and high-density lipoprotein and the ratio of total cholesterol: high-density lipoprotein), fasted blood glucose, insulin and a cardiovascular-related inflammatory marker (high-sensitivity C-reactive protein). Two tubes (serum – serum separator tube; plasma – EDTA) were collected and refrigerated for 20 min (so that the serum tube could clot) before being centrifuged together for 10 min at 2000 RCF at 4 °C. Resulting plasma and serum were pipetted and stored at −80 °C in 1 mL aliquots.

#### Resting blood pressure

2.7.8

Supine resting blood pressures on the right arm were taken every 3 min over a total of 15 min using an automated sphygmomanometer (Dinamap V100, GE, Healthcare, USA). This was done in a quiet dark room with the subject alone, undisturbed and lying supine. Mean arterial BP, SBP, DBP and HR of the last two assessments were recorded.

#### Cerebrovascular function

2.7.9

Cerebrovascular function was assessed by i). combining bilateral measures of cerebral artery blood flow velocity obtained using non-invasive, transcranial Doppler ultrasound techniques; and ii). cerebral artery diameter and blood flow velocity of the internal carotid and vertebral arteries using duplex ultrasound according to standardised approaches [47]. The reproducibility coefficient of variation of the resting assessment of middle cerebral artery velocity using transcranial Doppler was 4.5% from day-to-day within 71 subjects [48] and 1.5% for internal carotid artery diameter using duplex ultrasound for within-day variability [49]. In addition to resting baseline intra-cranial velocity and extra-cranial velocity and diameter recordings, four test conditions were implemented to challenge the cerebrovascular system and provide information relating to functional responsiveness to distinct types of stimulation. These four tests reflected cognition, dynamic cerebral autoregulation, cerebrovascular CO_2_ reactivity and exercise (described in more detail below; Supplementary Fig. 1). Intra-cranial velocity and extra-cranial velocity and diameter, as indices of cerebral blood flow, were assessed.

At the start of the session, the participant was fitted with a head frame (Marc 600, Spencer Technologies, Seattle WA, USA), with a 2-MHz ultrasound probe mounted on each temple, to facilitate imaging of the middle cerebral artery (right) and the posterior cerebral artery (left). A Finometer (Finometer Pro, Finapres Medicak Systems, Amsterdam ZO, The Netherlands) allowed continuous monitoring of beat-to-beat blood pressure via photoplethysmography. A three lead ECG was attached to monitor HR (BIO Amp CF, ADInstruments, New South Wales, Australia). Following instrumentation, the participant was seated on a semi-supine bench (incline of bench remained consistent to allow optimal reproducibility of blood vessel images) where the procedure was explained to them in detail. Once the participant was in position, a mouthpiece connected to a spirometer (Spirometer, ADInstruments, New South Wales, Australia) was placed in the participants mouth, with a nose clip, in order to measure expired gases (Gas Analyzer, ADInstruments, New South Wales, Australia) during baseline measures and all four testing conditions. A 5 min resting baseline was recorded, followed by 1 min of resting vertebral and internal carotid artery baseline (LabChart 7 software, AD Instruments, Sydney, Australia). The following tests were then conducted, always in the same order and always by the same sonographer in a given twin pair.

##### Cogstate

2.7.9.1

A battery of reliable and well-validated cognitive tests was administered to encompass a range of cognitive domains [50]. These tests were conducted by a trained researcher and test results were analysed by the same individual, blinded to testing order. The following tests were conducted:•Detection test- A 3 min test which provides a measure of psychomotor function reaction time and is assessed by speed of performance.•Identification test- A 3 min test which measures attention and choice reaction time via speed of performance.•Maze learning test- A 7 min test that measures executive function via total number of errors made during the task.•International shopping list test- A 5 min test that measures verbal learning and episodic memory. This is done by measuring the total number of correct answers in remembering the list on three consecutive trials, at a single session.•Two back test- A 4 min test which measures working memory via on-line monitoring, updating and manipulation of remembered information. This test is scored using accuracy of performance.•Set-shifting test- This test measures executive function or the ability to display flexibility using total number of errors in 7 min.•Modified chase task- This 4 min test measures executive function or response inhibition using speed of performance.•SF-12 health survey- This 12-item questionnaire takes approximately 2 min to complete and assesses health and well-being. Specific outcome measures include physical and social functioning, role limitations due to emotional problems, mental health, energy/vitality, pain, and general health perception.•PSQI- This 5 min survey provides a measure of the participants current sleep behaviour.•DASS21- This 3 min survey provides information on measures of depression, anxiety and stress.

##### Dynamic cerebral autoregulation

2.7.9.2

For this test, cerebral blood flow was assessed in response to different ‘doses’ of BP manipulation. Oscillations in BP were stimulated by a squat-stand stimulus of two different frequencies. First, participants standing manual BP was taken, followed by a 1 min standing baseline, prior to commencing 3 min of squat stands at a frequency of 0.33Hz. After the commencement of this test the participant was seated, allowing 5 min recovery, before they commenced a replica procedure at 0.66Hz. This methodological approach is in accordance with published guidelines on this technique [51]. Impairment in dynamic cerebral autoregulation is strongly linked to adverse clinical outcomes [52,53].

##### Cerebrovascular CO_2_ reactivity

2.7.9.3

This test measures a dose-response effect to different ‘doses’ of blood CO_2_, achieved by switching from room air to gas mixtures that contain differing concentrations of CO_2_. Impairment in cerebrovascular CO_2_ reactivity is an independent predictor of stroke risk and cognitive impairment [54,55]. The participant initially breathed room air for a 1 min baseline period before being connected to a Douglas bag containing a mixture of 3% CO_2_, 21% O_2_ and balanced N_2_. The participant continued to breath normally for 3 min, before the Douglas bag was disconnected, and the participant breathed normally for 2 min of recovery. The mouth piece was then removed, and the participant was given a 5 min break to allow full recovery before the next test. This process was repeated with a bag mixture of 6% CO_2_, 21% O_2_ and balanced N_2_.

##### Exercise

2.7.9.4

This test is used to assess cerebral blood flow to differing intensities of exercise, achieved by cycling for 2 min at three different Wattage. The participant was positioned semi-supine on a bench with their feet on a Monark biycle (Ergomedic 828 E, MONARK, Vansbro, Sweden), with the mouthpiece in. A 1 min baseline was recorded before the participant commenced their first 2 min stage at 60 W, followed immediately by 2 min at 90 W and again by 2 min at 120 W. The participant maintained their RPM between 50 and 60RPM throughout the entire 6 min test.

#### Conduit artery structure and function

2.7.10

A 10-MHz multifrequency linear array probe attached to a high-resolution ultrasound machine (T3300, Terason, Burlington, Massachusetts) was used to simultaneously assess brachial and femoral artery structure and function in accordance with the methods described by Thijssen in 2011 [56]. Common carotid artery (CCA) wall thickness and lumen diameter was also assessed.

##### Carotid artery wall thickness

2.7.10.1

Following an initial 15–20 min rest period, resting wall thickness and diameter of the left and right CCA was obtained using the high-resolution ultrasound machine (Supplementary Fig. 2). 10s longitudinal B-mode recordings of the middle, anterior and posterior (in that order) views of the CCA were obtained approximately 2 cm proximal to the carotid bifurcation. Settings were adjusted to focus on the superior and inferior walls of the CCA arterial lumen interface and the intima media adventitia [57].

##### Endothelium-dependent vasodilation: flow-mediated dilation

2.7.10.2

To assess endothelium-dependent vasodilation of the brachial and femoral arteries, the flow-mediated dilation (FMD) technique was used (Supplementary Fig. 3), described in more detail elsewhere [56]. The reliability of FMD tested ~7 days apart in healthy subjects has a high correlation (r = 0.82) [58]. In summary, a rapid inflation-deflation pneumatic cuff (D.E. Hokanson Inc., Bellevue, WA, USA) was wrapped around the left forearm, 2 cm distal to the olecranon process. A second larger cuff was positioned on the upper left thigh ~15 cm distal of the inguinal ligament, or ~5 cm proximal to the patella and patella tendon. The arterial-lumen interface was optimised for longitudinal B-mode images of the brachial and femoral arteries. Continuous Doppler pulse wave velocity of each artery was simultaneously obtained (by two expert vascular sonographers) using the lowest possible isonation angle (60°). Dynamic range and Doppler gain settings were consistent between machines, and specifications were replicated for each individual on repeat visits. The left arm was placed at the height of the heart in approximately 80⸰ abduction from the body. The arm was supported underneath the muscles and the hand slightly pronated in a relaxed position for the participant. The brachial artery was scanned in the middle or upper third of the arm, depending on positioning of the brachial artery bifurcation. The brachial artery was also scanned either through the biceps brachii or between the biceps and triceps brachii muscles, depending on which gave a cleaner image for analysis for that particular participant. The femoral artery was assessed in the proximal third of the thigh, at least 5 cm distal from the bifurcation, with the left leg in slight (<5°) lateral rotation. These anatomical specifications were noted at the initial testing session and replicated at the repeated visits.

A baseline scan was recorded for a period of 1 min to assess resting blood vessel diameter, shear rate and blood flow velocity. Both blood flow occluding cuffs were rapidly inflated to a suprasystolic pressure of 220 mmHg for 5 min. Recording resumed 30s prior to cuff deflation so that it wasn't missed and continued for 3 min post-deflation [59]. Peak artery FMD (absolute and %), shear stress, time to peak and artery diameter pre-post cuff were analysed as previously described [56,58,59].

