
## Planned statistical analysis

3

Statistical analyses are to be performed with SPSS 20.0 (IBM Australia Ltd, New South Wales, Australia) and STATA 11 software (StataCorp, College Station, Texas). All data will be reported as group means with confidence intervals, with default statistical significance assumed at *P* < 0.05. Cross-sectional results for each outcome measure refer to baseline entry (week 0) data. Response to training data is post minus pre for END and RES training. Normality of groups (MZ and DZ) will be assessed via Shapiro-Wilk test of normality where normality of spread is assumed at *P* > 0.05. Between-group (MZ vs DZ) differences will be assessed with the conservative non-parametric Mann-Whitney *U* test and regression models including the single covariate zygosity (MZ/DZ), fitted using a generalised estimating equation (GEE) approach to account for correlation of twins within-pairs. The effect of the exercise interventions on each outcome measure will be assessed using a linear mixed models approach.

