The primary objective of the current study is to estimate the MZ and DZ correlations and the variance components A, C and E for each outcome measure cross-sectionally, and in response to exercise training (END and RES). In STATA mixed models effects will calculate intraclass correlation coefficients (r) for MZ and DZ twin pairs. Covariates to be adjusted for (e.g. sex, fat-free mass, VO_2max_, baseline data) will depend on the primary outcome measure. The subsequent rMZ and rDZ, and their respective P-values and 95% confidence intervals will be presented. Differences between intraclass correlations (rMZ vs rDZ) will be assessed using the likelihood-ratio test in STATA to compare mixed effects models constraining covariances for MZ and DZ pairs to be equal with models allowing different covariances for MZ and DZ pairs [69]. If the model allowing different MZ and DZ covariances are significantly better, and rMZ are significantly different to rDZ, A, C and E will then be calculated from the estimates of the DZ covariance and the additional MZ covariance, and confidence intervals for A, C and E will be estimated using the delta method. When rMZ and rDZ are not significantly different then a single model that includes all twin pairs but constrains the covariance to be equal for MZ and DZ pairs will be used in STATA to calculate C and E components only, and their respective 95% confidence intervals. An additional model which estimates covariance for MZ twins but fixes the DZ covariance to be zero will test if the estimated correlations suggest that the equal environments assumption has been violated.

Secondary objectives of this study will be addressed using the individual change with training (END and RES) results for each outcome measure. Response rates for each modality can be derived as a percentage of positive responses (>0) and compared against one another by a Z-test. Concordances can be derived as the percentage of individuals who positively respond to both exercise training modalities (Supplementary Fig. 5). In a similar way to the correlation analyses, within-twin pair concordances for MZ and DZ can be derived for each exercise intervention and compared to each other.

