### Sample size and power

3.2

Power analysis is based on our primary outcome measures which are highly specialized and sensitive; vascular function (FMD), cardiac and cerebrovascular adaptation. Our cardiac publications [6,8,9] have reported significant effects in fewer subjects (n = 10 and n = 13 per group) than we recruited in the present study; we observed highly significant differences utilising highly sensitive MRI. Regarding cerebral measures, previous publications and our pilot work demonstrate that cerebral blood flow is increased in older individuals (n = 9, 65–78 yrs) by 10% after intervention. Our previous twin study publications in a paediatric population [24,31] cross-sectionally revealed FMD correlations of 0.6 and 0.38 in MZ and DZ twin pairs, respectively, in a smaller sample size of 22 (11 pairs) per group [24]. In addition, this study applied an exercise intervention (8 weeks) shorter than the current study (12 weeks), and produced correlations of 0.74 and 0.37 for FMD responses in MZ and DZ groups (n = 24–6 pairs per group) [31]. A power analysis (G*Power v3.1.2), performed using the predicted correlations for rMZ = 0.80 and rDZ = 0.30, assuming alpha = 0.05, indicates that a sample size of 23 individuals in each group provides 80% power.

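### The single sample-size input of rMZ 0.80 against rDZ 0.30 is too optimistic for FMD on the protocol's own figures, so the stated 80% power should not be read as applying to FMD

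*Protocol article*

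**What the plan says.** Section 3.2 (Sample size and power) opens: "Power analysis is based on our primary outcome measures which are highly specialized and sensitive; vascular function (FMD), cardiac and cerebrovascular adaptation". It then gives one calculation, "performed using the predicted correlations for rMZ = 0.80 and rDZ = 0.30, assuming alpha = 0.05", and concludes that "a sample size of 23 individuals in each group provides 80% power". It does not say whether the two correlations refer to week-0 values or to training responses, or to which of the named outcomes.

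Section 3 (Planned statistical analysis) sets the primary objective as follows: "estimate the MZ and DZ correlations and the variance components A, C and E for each outcome measure cross-sectionally, and in response to exercise training". The response is a simple difference: "Response to training data is post minus pre for END and RES training". rMZ and rDZ are compared by a likelihood-ratio test. A, C and E are calculated only if that test is significant; otherwise only C and E are estimated. Baseline data are listed among possible covariates.

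Two other places bear on the input. Section 2.7.10.2 says of FMD: "The reliability of FMD tested ~7 days apart in healthy subjects has a high correlation (r = 0.82". Section 3.2 itself cites earlier FMD twin correlations of 0.60 (MZ) and 0.38 (DZ) cross-sectionally in 11 pairs per group. It also cites 0.74 and 0.37 for the response to training, in what appears to be about 6 pairs per group.

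**The concern.** Measurement error that co-twins do not share pulls an observed twin correlation below the true one, and the reliability of the measure sets the ceiling. A reliability of 0.82 leaves almost no room above an assumed rMZ of 0.80. A difference of two such measurements is usually less reliable than either one. The assumed contrast of 0.80 against 0.30 is also wider than either FMD contrast the protocol cites.

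The primary objective is at stake. Under the rule in section 3, a non-significant rMZ versus rDZ test removes A from the reported model and leaves C and E. If power for FMD response is well below 80%, that outcome can arise from the measure and the sample size even when the response is strongly heritable. A reader relying on the stated 80% could then take it as evidence against a genetic contribution.

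**Working it through.** **1. The plan's own figure.** Inputs from section 3.2: rMZ 0.80, rDZ 0.30, alpha 0.05. Fisher z for two independent correlations:

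n per group = 2 × [(z_alpha + z_power) / (atanh 0.80 − atanh 0.30)]² + 3

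atanh 0.80 − atanh 0.30 = 1.0986 − 0.3095 = 0.7891. One-sided: 2 × [(1.645 + 0.842)/0.7891]² + 3 = 22.9, so 23, which matches. Two-sided: 28.2, so 29. In this formula n counts pairs. Sidedness and the counting of individuals are separate matters, and nothing below rests on them. The question here is the input pair.

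**2. Week 0.** Ceiling on rMZ = reliability = 0.82. An observed 0.80 needs a true MZ correlation of 0.80/0.82 = 0.976. The protocol's earlier cross-sectional value is 0.60.

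**3. Training response, raw difference.** Let p be the observed pre-post correlation of FMD. With equal pre and post variances and independent errors, the reliability of the difference, and so the ceiling on rMZ, is (0.82 − p)/(1 − p). The documents do not give p, so a range is assumed:

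| p | ceiling on rMZ |
|---|---|
| 0.1 | 0.80 |
| 0.3 | 0.74 |
| 0.5 | 0.64 |
| 0.7 | 0.40 |

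Setting the ceiling at 0.80 or more gives p ≤ (0.82 − 0.80)/(1 − 0.80) = 0.10, and even then MZ twins' true changes must agree perfectly. Put another way, the variance of true change would have to be at least 0.80 × 2 × 0.18/0.20 = 1.44 times the total baseline variance.

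**4. Training response, adjusted for baseline.** The ceiling becomes 1 − 0.18(1 + p²)/(1 − p²): 0.78 at p = 0.3 and 0.70 at p = 0.5. It reaches 0.80 when p² ≤ (0.20 − 0.18)/(0.20 + 0.18), so p ≤ 0.23.

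**5. Power at the protocol's own FMD correlations.** No value of p is needed here. The likelihood-ratio column is a simulated two-sided 5% test of equal against different MZ and DZ covariances with a common mean and variance. The Fisher z column is also two-sided. Each range or pair covers 23 pairs per group and the 31 MZ and 14 DZ pairs of Table 1.

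| rMZ/rDZ | source | likelihood ratio | Fisher z (23 per group; 31/14) |
|---|---|---|---|
| 0.80/0.30 | plan's input | about 78–87% | 70%; 60% |
| 0.74/0.37 | earlier FMD response | about 53–58% | 43%; 35% |
| 0.60/0.38 | earlier FMD cross-sectional | about 18–22% | 15%; 13% |

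The planned type of test reaches roughly 80% at the plan's own input, so the shortfall in the lower rows comes from the input.

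**6. Power at the ceiling.** For a fully additive genetic response (rMZ at the raw-difference ceiling, rDZ at half of it), likelihood-ratio power with 31/14 pairs is about 54% at p = 0.3 and 31% at p = 0.5. With 23 pairs per group it is about 58% and 37%. Part of that fall comes from setting rDZ at half of rMZ: at 23 pairs per group, 0.80/0.40 already gives about 75%.

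**The case against.** The strongest objection is that a reader might infer from 0.82 that an rMZ of 0.80 is out of reach for FMD response and that 80% power cannot hold. The documents do not support that. The figure 0.82 exceeds 0.80, so week 0 is not excluded. For the response, the step needs a value of p above 0.10 that the documents do not give, with equal variances and independent errors. Baseline adjustment relaxes the threshold to about 0.23. Section 3.2 does not tie 0.80/0.30 to FMD response, and the reported MRI test-retest correlations of 0.93–0.99 (2.7.11.1) make this ceiling much weaker for cardiac outcomes. All of this stands and limits the point.

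Errors may also be shared within a pair, since twins trained together and were assessed within a week of each other. Shared error does raise the rMZ ceiling. At p = 0.5, an error correlation of (0.80 − 0.64)/(1 − 0.64) = 0.44 restores rMZ to 0.80. It also lifts rDZ to 0.32 + 0.36 × 0.44 = 0.48, and power at 0.80/0.48 is only about 60%. The planned contrast is not restored.

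The earlier response value of 0.74 shows that a high correlation has been observed. With 6 pairs its 95% interval runs from about −0.18 to 0.97, so it neither establishes nor rules out 0.80. It came with an rDZ of 0.37, not 0.30.

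Finally, no passage says that a non-significant test will be read as absence of a genetic effect, and the Introduction allows for reporting familial aggregation where effects cannot be separated. The misreading is a risk, not a stated intention.

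**Conclusion.** The point holds as a criticism of an optimistic input, not of an impossible one. One pair of correlations, 0.80/0.30, underlies the 80% power for outcomes that include FMD. For FMD, that pair sits against a reliability of 0.82 with no visible allowance for differencing, and it is wider than both contrasts the protocol cites. Without assuming any p, likelihood-ratio power is about 53–58% at the cited response correlations and 18–22% at the cited cross-sectional ones. With p assumed between 0.3 and 0.5 and a fully additive response, it is roughly 31–58%.

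A claim that the FMD response test would usually be non-significant also goes too far: at p = 0.3, power is slightly above one half.

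The power figures rest on the small earlier samples, or on the assumed p with equal variances and unshared errors. The reliability comes from a cited source and may differ in this sample.

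**What to change.** In section 3.2:

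- Replace the single input for FMD with separate predicted correlations for week-0 FMD and for FMD response, consistent with the 0.82 reliability and the cited 0.60/0.38 and 0.74/0.37.
- Restate the FMD power for each as a range over assumed p, in place of the single 80%.
- Add that a non-significant rMZ versus rDZ comparison for FMD response is not evidence against a genetic contribution.

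Estimating p from the trial's pooled data, or printing the ceiling beside the reported correlations, is optional. The former would be a retrospective calculation and should be labelled as such.

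The change needs wording and a short calculation, with no new data. Its cost is a less favourable power statement for FMD.
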